#### Recruitment {15}

Building on the lessons learned from the HIV self-testing pilot study, MAC will use social media to promote this study. Promotional materials will be distributed via various social media platforms, including digital fliers and posters (approved by the Medical Research & Ethics Committee, Ministry of Health, Malaysia), as well as online talk shows and videos that will provide basic information about hepatitis C, why testing is important and details about the HCV self-testing study, including information on how to enrol. Participants do not need to be enrolled in the HIV self-testing pilot study to be eligible for this HCV self-testing impact study.

### Assignment of interventions: allocation

#### Sequence generation {16a}

Prior to study enrolment, a list of potential study IDs in ascending numerical order will be generated and randomised by computer to either an intervention or the control group.

#### Concealment mechanism {16b}

Due to the methods of online enrolment and randomisation used, there is no additional concealment mechanism used.

#### Implementation {16c}

As shown in Fig. 1, study participants will be recruited through an existing online platform called JomTest, which currently offers HIV self-testing. Interested participants will sign up and proceed to study eligibility screening; if they are eligible, they will be invited to provide informed consent. After providing consent, enrolled study participants will complete a baseline survey to collect data on their demographics and knowledge of and attitudes towards HCV testing.

**Fig. 1 Fig1:**
[figure not shown]
Study flow diagram

Upon enrolment, study participants will be assigned study IDs in a consecutive fashion by the online platform, thereby completing their assignment to a study group. The randomised number encodes a participant’s assignment to one of the study arms, according to the randomisation schedule generated prior to the study by the FIND statistician.

### Assignment of interventions: blinding

#### Who will be blinded {17a}

Participants, researchers and site staff will not be blinded, as this would be impossible due to obvious differences between the two groups (receiving an HCV self-test versus being referred to facility-based testing).

#### Procedure for unblinding if needed {17b}

As this study is not blinded, there is no unblinding procedure.

### Data collection and management

#### Plans for assessment and collection of outcomes {18a}

Participants will complete the baseline, follow-up #1 and follow-up #2 surveys via the online platform (supplementary annex 3). The baseline survey will assess participants’ current knowledge of hepatitis C, including risk factors for contracting hepatitis C, as well as gather information on their current behaviours that may be related to risk factors.

Follow-up survey #1, to be taken 2 to 4 weeks post-enrolment, will ask the participant to report if they have conducted the HCV test and, if so, to provide the results of the test. If the participant reports having taken the test, they will be asked to answer questions relating to their perception of the testing experience and what actions they took following their test result. If the participant reports that they have not yet taken the test, they will be asked questions about why they have not yet taken the test. This survey will also gather information from all participants on their current behaviours that may be related to risk factors for HCV.

Follow-up survey #2, to be taken 4 to 8 weeks post-enrolment, will ask the participant to report if they have taken the HCV test (if they have not already reported taking the test in follow-up survey #1) and, if so, to provide the results of the test. If the participant reports having taken the test, they will be asked to answer questions relating to their perception of the testing experience and what actions they took following their test result. If the participant reports that they have not yet taken the test, they will be asked questions about why they have not yet taken the test. For participants who reported taking the HCV test in follow-up survey #1, follow-up survey #2 will start by gathering information on what actions the person has since taken with regards to seeking further HCV care (if their HCV test was positive). This survey will also gather information from all participants on their current behaviours that may be related to risk factors for HCV.

Data relating to costs will be gathered from a provider’s perspective and will be obtained by conducting a desk review of the costs incurred in the study. These costs will include aspects such as human resources, shipping, and maintaining the online platform.

#### Plans to promote participant retention and complete follow-up {18b}

All participants will be sent a reminder for follow-up survey #1 approximately 2–4 weeks from their day of enrolment. A second follow-up survey will be sent 2 to 4 weeks after the closure of the first survey. Up to three reminders will be sent if a survey has not been completed. To increase the likelihood of participants reporting whether they took the HCV antibody test, participants will receive 20 Malaysian ringgit (~ 5 USD) via electronic voucher or electronic wallet top-ups for completing follow-up survey #1 and an additional 20 Malaysian ringgit for completion of follow-up survey #2.

#### Data management {19}

To ensure information security and confidentiality, the online platform will use verified access to the site, data encryption between personal computers and the website, and encryption of all databases. Information will only be available to users registered with a login and a secure password. Completed informed consent forms and the data recorded via the online platform will be protected with a multilayer security mechanism. Each member of the study team personnel who has access to the files will be assigned appropriate levels of access. Only designated study team personnel will have access to personal identifying information, and these data will not be accessible to the study sponsor.

#### Confidentiality {27}

Participants will be assigned a unique identifier, generated by the study sponsor. Any participant record or dataset that is transferred to the study sponsor will include this identifier only; participant names or any information that would render the participant identifiable will not be transferred.

#### Plans for collection, laboratory evaluation and storage of biological specimens for genetic or molecular analysis in this trial/future use {33}

As there will be no collection of biological specimens for this study, there is no opportunity for genetic or molecular analysis.

## Statistical methods

### Statistical methods for primary and secondary outcomes {20a}

Data will be analysed using R (version 4.1 or higher). A summary of the statistical analyses that will be completed by the endpoint is shown in Table 2. These analyses will be conducted among the group of participants who received the oral fluid-based HCV self-test with the control group and the group of participants who received the blood-based HCV self-test with the control group.

**Table 2 Tab2:** Statistical analyses to be completed by the endpoint

Endpoint	Statistical analysis methods
1.1 The number and the proportion of participants who report completing the HCV antibody testing in the intervention group 1.2 To assess whether the proportion of participants who report completing the HCV antibody testing in the intervention group is greater than that reported by the participants in the control group by a margin of 20%	Descriptive statistics: Calculation of proportions with 95% CI of the difference in proportions will be evaluated by using the R function prop.test from the “stats” package, which relies on Wilson’s score method. Test of proportions: Two-sided test with a margin of 20%, implemented with the R function “stats::prop.test” with the following hypotheses: *H*_0_: *p*_fo,*I*_ − *p*_fo,*C*_ ≤ 20% *H*_A_: *p*_fo,*I*_ − *p*_fo,*C*_ > 20% where proportions are defined as *p*_*x*,*y*_ [*x* = investigated outcome (fo, pt, ref, trt), *y* = element of {intervention, control}]) comparing the proportion of individuals reporting HCV test results in the intervention versus control groups and between intervention groups. The differences will be reported together with their confidence intervals and the *p*-value related to the statistical comparison mentioned above. The alpha level will be set at 0.025 (2 two-sided tests with an alpha level of 0.05, with the application of Bonferroni correction).
2.1 Number and proportion of HCV antibody-positive individuals made aware of their status in the intervention versus the control group	Descriptive statistics: Statistical testing comparing the numbers of individuals in the intervention versus control groups and between the intervention groups. For details, see the methodology described for endpoint 1.2.
2.2 Number and proportion of HCV antibody-positive individuals who are referred for and complete HCV RNA confirmatory testing in the intervention versus control group	
2.3 Number and proportion of HCV RNA-positive individuals who begin treatment in the intervention versus the control group	
2.4 Analysis of survey responses using proportions and means	Descriptive statistics for survey responses (e.g. proportions, means), as appropriate for the type of response.
2.5 Cost per test completed and cost per person diagnosed (serology, RNA) in the intervention versus control groups	Ingredients-based cost calculation approach.

In a sensitivity analysis, a possible confounding in terms of the time of proband’s actions will be evaluated by analysing the proportions as events by means of Kaplan-Meier analyses with the advantage that dropouts are taken into account as censored values in addition.

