#### Participant timeline {13}

The participant timeline is presented in Table 1.

**Table 1 Tab1:** Participant timeline

Procedure	Enrolment	Test results	Follow-up #1	Follow-up #2
	Day 0	Weeks 2–4	Weeks 2–4	Weeks 4–8
Inclusion and exclusion criteria via the online survey	X			
Informed consent via the online form	X			
Demographic information; Knowledge, Attitudes and Practices (KAP) survey; risk behaviour via the online survey	X			
Completion of follow-up survey #1 regarding the perceptions of testing processes, uploading of test results, KAP and further linkage to care (if applicable)		X	X	
Completion of follow-up survey #2 regarding the risk behaviours and further linkage to care (if applicable)				X
Linking of data of RNA test results and treatment initiation (if applicable)			X	X
Adverse events/severe adverse events/social harms review	X	X	X	X
Cost data collection/analysis	X	X	X	X

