#### Sample size {14}

The study will enrol a minimum of 750 participants who meet the inclusion criteria. There will be a minimum of 250 participants who receive an oral fluid-based HCV self-test, 250 participants who receive a blood-based HCV self-test and 250 participants in the control group. The study is powered to detect at least a 20% between-group difference in HCV antibody self-testing between the intervention group and the control group, based on 80% statistical power and an alpha level of 0.05. As this study is one of the first to explore the impact of an HCV self-testing distribution model, there are no references available to draw on for the expected difference in between-group uptake of antibody testing rates. The use of a 20% between-group difference in HCV antibody testing uptake is based on expert opinion, according to previous experiences with HIV self-testing and the increases in the uptake of testing seen with the use of HIV self-testing [15].

For the primary objective, the null hypothesis is that there is no significant difference in the proportion of individuals reporting HCV test results in the intervention versus control groups. The alternative hypothesis is that home-based HCV self-testing in the intervention group will significantly increase the proportion of individuals reporting HCV test results.

The study is not powered to detect significant differences in the secondary objectives. However, similarly to the primary objective, the null hypothesis would be no significant difference between the intervention versus control groups, with the alternative hypothesis being that home-based HCV self-testing will result in significantly higher numbers of HCV-infected individuals being diagnosed, linked to care and treated, making it a cost-effective approach to HCV case-finding and elimination.

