### Methods for additional analyses (e.g. subgroup analyses) {20b}

There are no additional analyses planned for this study.

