## Discussion

### Limitations

The study has some important limitations that will be considered and described in the study report. The foremost of these is due to the fact that it is important not to mix different types of tests (oral vs blood) at the same timeframe within the same community which would likely create disruptions and potentially hamper the study, we were unable to enact a 3-arm trial. Rather, the study allocates one type of test kit for the first 250 participants randomised to the intervention group and another type of test kit for the next 250 participants randomised to the intervention group. The control group will be recruited throughout the length of the study to minimise any selection bias over time. Additionally, because enrolment will be conducted via an online platform, the study population will comprise individuals who have access to the Internet and are Internet literate. This may exclude individuals who could also benefit from HCV self-testing but who are unable to access the Internet. Uptake of testing in the control arm may be affected by the geographical location of the participant and the distance to their nearest testing centre. Moreover, the ongoing COVID-19 pandemic could affect the participants’ willingness to visit a healthcare facility, which may have a negative impact on the uptake of testing in the control arm and the uptake of treatment in both the intervention and control arms. Finally, the questionnaires have a multiple-choice design that may not capture some important context-specific aspects.

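### The primary comparison is fixed as an unadjusted two-proportion test although baseline data are collected; a pre-specified covariate-standardised risk difference would give a modest gain in precision against the 20-point margin

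*Protocol article*

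**What the plan says.** All references are to the Protocol article.

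- **Method.** Table 2, under Statistical methods for primary and secondary outcomes {20a}, gives the primary estimate and interval: "95% CI of the difference in proportions will be evaluated by using the R function prop.test". The test is described as "Two-sided test with a margin of 20" percent. Its null hypothesis is that intervention minus control is at most 20 points. No covariate is named.
- **Comparisons and alpha.** Each kit group is compared with control. On significance, Table 2 states: "The alpha level will be set at 0.025", by Bonferroni correction for two tests.
- **Other analyses.** The one sensitivity analysis is a Kaplan-Meier analysis of timing. Section {20b} adds: "There are no additional analyses planned for this study".
- **Baseline data.** The Participant timeline {13} lists, at enrolment: "Demographic information; Knowledge, Attitudes and Practices (KAP) survey; risk behaviour via the online survey". Implementation {16c} places the baseline survey after consent.
- **Possible predictors.** Limitations says that uptake in the control arm may be "affected by the geographical location of the participant and the distance to their nearest testing centre". It does not say this of the intervention arm, whose kits are mailed.
- **Size.** Sample size {14} sets at least 250 participants per kit group and 250 controls, "based on 80% statistical power and an alpha level of 0.05", for a 20-point difference.
- **Allocation.** Sequence generation {16a} describes a computer-randomised list of study IDs and mentions no stratification.

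**The concern.** A two-sample proportion test cannot use baseline information. If baseline variables predict who completes a test, leaving them out gives a wider interval for the risk difference than the same data could support.

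This would hardly matter if the test were against a difference of zero, where 250 per group has ample power for a 20-point effect. Table 2 tests against 20 points instead. There, power depends on how far the true difference exceeds the margin, and it can be moderate at plausible values. A somewhat narrower interval could then decide whether the lower limit clears the margin. Adjustment would also allow for chance imbalance between groups in the chosen variables, since no stratification is described.

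**Working it through.** **Inputs from the document.** 250 per kit group and 250 controls ({14}); margin 20 points and alpha 0.025 per comparison, two-sided (Table 2), so z = 2.241.

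**Inputs assumed.** The document gives no uptake rates and no prognostic strength for any covariate. I take control uptake 30%, true difference 30 points (intervention 60%), and a share of outcome variance explained by baseline covariates (R²) of 0.05 to 0.15.

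**Step 1. The plan's own figure.** Sample size {14} says: "The study is powered to detect at least a 20% between-group difference in HCV antibody self-testing". Against a null of zero, 80% power for 20 points needs at most 97 per arm at two-sided alpha 0.05, or 118 at 0.025, for control rates from 10% to 70% (no continuity correction). With 250 per arm, power is at least 98.9% at either alpha. The stated 250 is therefore not reproduced as a requirement, and on that null extra precision would buy almost nothing.

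**Step 2. Unadjusted power against the margin.**

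SE = sqrt(0.60×0.40/250 + 0.30×0.70/250) = sqrt(0.00096 + 0.00084) = 0.0424

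Power = Φ((0.30 − 0.20)/0.0424 − 2.241) = Φ(2.357 − 2.241) = Φ(0.116) = 54.6%

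The same calculation gives 54.6% at control uptake 40%, and 59.0% at 20% or 50%. At control uptake 30%, power is 14.2% for a true difference of 25 points and 91.1% for 35 points.

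**Step 3. Covariates that predict in both arms.** Variance is multiplied by (1 − R²): Power = Φ(0.10/(0.0424×sqrt(1 − R²)) − 2.241).

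| R² | SE | Power | Equivalent sample, 1/(1 − R²) | 95% CI half-width (1.96×SE) |
|---|---|---|---|---|
| 0 | 0.0424 | 54.6% | 1.00 | 8.3 points |
| 0.05 | 0.0414 | 57.0% | 1.05 | 8.1 points |
| 0.10 | 0.0402 | 59.6% | 1.11 | 7.9 points |
| 0.15 | 0.0391 | 62.4% | 1.18 | 7.7 points |

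**Step 4. Covariates that predict in the control arm only.** This is the case that Limitations describes for location and distance. For 500 participants split 1:1, the best attainable variance is

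[0.24/0.5 + 0.21×(1 − R²)/0.5 + 0.21×R²]/500,

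where R² now refers to the control arm. The last term appears because such a covariate also makes the effect vary between participants.

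| Control-arm R² | Fall in variance | Power |
|---|---|---|
| 0.05 | 1.2% | 55.2% |
| 0.10 | 2.3% | 55.7% |
| 0.15 | 3.5% | 56.3% |

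For scale, suppose half the controls live near a centre with 45% uptake and half live far away with 15%. The control-arm R² is then 0.15²/0.21 = 0.107, so even a strong distance effect cuts the variance by only about 2.5%.

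**Step 5. What adjustment cannot do.** At a true difference of exactly 20 points, power is Φ(0 − 2.241) = 1.25% whatever R² is.

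**Step 6. Enrolment phase as a covariate.** The first 250 intervention participants get the oral kit and the next 250 the blood kit, while controls are recruited throughout. In each kit-versus-control comparison, phase adjustment leaves mainly the concurrent controls, about 125 if enrolment is even. Then SE = sqrt(0.24/250 + 0.21/125) = 0.0514 and power = Φ(1.946 − 2.241) = 38.4%. Phase adjustment costs precision.

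**The case against.** The strongest case against is that nothing here is wrong. An unadjusted difference in proportions is valid under the computer-generated allocation and matches the stated endpoint. Covariates are often left to the analysis plan, which is not shown, and section {20b} may refer only to subgroup-type analyses. The R² range is assumed. All of this stands, and it limits the point to an efficiency suggestion. What remains is that the article does not leave the primary method open: it names a specific unadjusted function.

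Three stronger readings are tempting, and the document does not support them.

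- *That the protocol identifies location and distance as drivers of uptake and ignores them.* Limitations offers them only as possible influences, and only in the control arm. Distance is not among the variables listed as collected. Step 4 shows how little a control-arm predictor yields.
- *That precision equal to 5% to 18% more participants is being given away.* That follows only if R² of 0.05 to 0.15 holds in both arms. In the control-arm case the equivalent gain is about 1% to 4% (1/(1 − 0.012) to 1/(1 − 0.035)).
- *That any baseline adjustment is free, including enrolment phase.* Step 6 shows the opposite for phase. It bears on calendar-time bias from giving the kits in sequence, which is a separate question.

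**Conclusion.** The point holds as a minor, worthwhile improvement. The planned analysis is valid but leaves out baseline data that the trial collects, and power against the 20-point null is not saturated. In the reference scenario the gain is about 2 to 8 percentage points of power (54.6% to between 57.0% and 62.4%) if covariates predict in both arms, and about 1 to 2 points (to between 55.2% and 56.3%) if they predict among controls only. These figures rest on assumed uptake of 30% v 60%, assumed R² of 0.05 to 0.15, the normal approximation and no missing outcomes. The direction of the gain is well supported; its size cannot be derived from the document.

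A reader might infer that adjustment rescues the power of the margin test. It does not. The larger weakness is that the design difference in {14} equals the margin in Table 2, and that must be resolved on its own.

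**What to change.** Before the data are analysed:

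1. Pre-specify a short list of baseline variables already collected, for example age, key-population group, and baseline testing practice or risk behaviour. Add location only if it is recorded and available to the analyst.
2. For each kit-versus-control comparison, fit a logistic model with arm and these variables. Average the predicted probabilities under each arm over all participants in the comparison to obtain a standardised risk difference. Form its interval by the delta method or bootstrap at the planned alpha, and compare it with the margin.
3. Report the unadjusted difference as supportive.
4. Leave enrolment phase out of this list and state separately how calendar time will be handled.

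The cost is a sentence or two in the analysis plan and a few lines of R. No new data are needed if the list is confined to variables already collected. The scale and margin of the primary comparison do not change.

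### The R function named for the primary test cannot test a 20-point margin: it tests equality, and its p-value would be significant in about 99% of trials when the true difference is exactly 20 points

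*Protocol article*

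**What the plan says.** In Statistical methods {20a}, Table 2, endpoint 1.2 is a "Two-sided test with a margin of 20%, implemented with the R function" stats::prop.test, "with the following hypotheses": H0, intervention minus control at most 20%; HA, intervention minus control more than 20%. On reporting, the same cell states: "The differences will be reported together with their confidence intervals and the" p-value belonging to that comparison. On error control: "The alpha level will be set at 0.025 (2 two-sided tests with an alpha level of 0.05", Bonferroni-corrected).

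On the interval, Table 2 says: "Calculation of proportions with 95% CI of the difference in proportions will be evaluated by using the R function prop.test", and attributes this to Wilson's score method.

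The text above the table sets out kit-specific comparisons: "These analyses will be conducted among the group of participants who received the oral fluid-based HCV self-test with the control group", and likewise for the blood-based kit. Sample size {14} plans at least 250 on the oral-fluid kit, "250 participants who receive a blood-based HCV self-test and 250 participants in the control group". Outcomes {12} repeats the 20% margin as part of the primary outcome, whereas Sample size {14} states a null of no difference. Endpoint 2.1 refers back to the method of endpoint 1.2.

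**The concern.** A null of at most 20 points and a null of zero are different hypotheses and need different test statistics. Table 2 states the first and names software that, with two groups, tests the second. The hypotheses, the function and the p-value to be reported are all fixed in one cell, so this is not detail left to an analysis plan.

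At stake is the main confirmatory claim. An analyst who follows the cell would print an equality p-value beside a hypothesis of more than 20 points, and a difference well short of 20 points could be published as significantly above it. Because endpoint 2.1 borrows the same method, the problem reaches beyond the primary outcome.

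Two smaller errors sit in the same cell. The test is called two-sided although HA points one way, and the interval method is named wrongly.

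**Working it through.** **Inputs.** 250 per kit group and 250 controls (Sample size {14}); alpha 0.025 per comparison and margin 0.20 (Table 2). Control uptake is not given, so I assume 5% to 75%.

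**1. The plan's own figure.** Sample size {14} gives 250 per group for 80% power to detect 20 points at alpha 0.05. Under an equality null the least favourable case is 60% against 40%:

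n = [1.96·√(2·0.5·0.5) + 0.8416·√(0.24 + 0.24)]² / 0.20² = (1.386 + 0.583)² / 0.04 ≈ 97 per group

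(118 at alpha 0.025). So 250 is not reproduced; under equality it gives 98.9% to 100% power at alpha 0.025. Under Table 2's margin null, a true 20 points is the boundary of H0, where the rejection rate is about 1.25%. There, 80% power needs a true difference of about 31.5 to 33 points (control uptake 10% to 50%). For example, with 73% against 40%: 0.20 + (2.241 + 0.842)·√((0.1971 + 0.24)/250) = 0.20 + 0.129 = 0.329.

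**2. What the function does (R 4.3.3).** Its arguments are x, n, p, alternative, conf.level and correct.
- The default call with two groups is labelled a test for equality of proportions.
- Setting the alternative to greater still tests equality.
- p = 0.2 stops with an error, because p must have the same length as x and n.
- p = c(0.6, 0.4) tests two fixed proportions on 2 degrees of freedom, not a difference.

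**3. Worked example, 150/250 against 100/250 (difference exactly 0.20).**
- prop.test: pooled proportion 0.5, expected count 125 in each of four cells, X² = 4·(25 − 0.5)²/125 = 19.208, p = 0.0000117.
- Margin test: z = (0.20 − 0.20)/SE = 0, one-sided p = 0.5.

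**4. How often the equality p-value would be significant.** Exact binomial enumeration, 250 against 250, continuity-corrected test, two-sided alpha 0.025, counting results in favour of the intervention. The last column counts trials where the lower limit of prop.test's own 97.5% interval for the difference exceeds 0.20.

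| Control uptake | p significant, true difference 20 points | p significant, true difference 10 points | CI lower limit > 0.20, true difference 20 points |
|---|---|---|---|
| 5% | 100% | 92.4% | 0.8% |
| 10% | 99.97% | 78.8% | 0.9% |
| 20% | 99.6% | 59.6% | 1.1% |
| 30% | 98.9% | 50.5% | 1.1% |
| 40% | 98.4% | 47.4% | 1.2% |
| 50% | 98.9% | 47.4% | 1.1% |
| 60% | 99.6% | 50.5% | 1.1% |
| 70% | 99.97% | 59.6% | 0.9% |
| 75% | 100% | 67.7% | 0.8% |

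Both true differences lie within H0, so the nominal rate in the upper tail is at most 0.025/2 = 1.25%. The equality p-value becomes significant at an observed difference of about 8 to 10 points (for example 44/250 against 25/250, or 126/250 against 100/250).

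**5. Other group sizes.** With both kits pooled (500 against 250), the rate at a true 20 points is 99.8% to 100%. If each kit were compared only with about 125 concurrent controls (my assumption), it is 91% to 99.9% for control uptake of 5% to 70%.

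**6. The interval.** For two groups the R source computes the difference ± [z·√(Σ p(1 − p)/n) + 0.5·Σ(1/n)], that is, Wald with continuity correction. In the example: 0.20 ± (1.96·0.04382 + 0.004) = 0.1101 to 0.2899, which is what R prints. The Wilson-based interval for a difference (Newcombe) is 0.1126 to 0.2831. In prop.test, Wilson's score method applies only to the one-sample interval.

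**The case against.** The strongest reply has three parts.

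- **The p-value may never be misused.** The function cannot produce the p-value that Table 2 asks for, and its output is headed as an equality test, so a careful analyst would notice. This is fair: the 99% arises only if the default call is run and its p-value is reported against the stated hypotheses. But that is the call the table names, and the table requires a p-value for that comparison.
- **The interval protects the reader.** The difference is reported with its confidence interval, and in the example 0.110 to 0.290 plainly includes 0.20. Judging the margin by the lower limit would hold the error at 0.8% to 1.2% with a 97.5% interval, or 1.7% to 2.4% with a 95% interval. This also stands as arithmetic, but the protocol states no such rule.
- **Equality may be what was meant.** Under the null in Sample size {14}, prop.test is a proper test and 99% at 20 points is simply power. Then the margin hypotheses in Table 2 and the margin in Outcomes {12} are wrong instead. The reply settles which text to change, not whether to change it.

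The objection does succeed on scale for the smaller points. The Wilson misstatement moves the limits by less than 1 point in the example, and the word two-sided is mainly a matter of consistency.

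**Conclusion.** The concern holds, and the p-value is the serious part. The two-sample prop.test cannot test the hypotheses written beside it. Used as named, it would report a significant result in 98.4% to 100% of trials at the boundary of H0, against a nominal 1.25%, and in 47% to 92% at a true difference of 10 points. These figures assume 250 per group, alpha 0.025 and control uptake of 5% to 75%; the conclusion does not depend on where in that range uptake falls. Table 2 is wrong as written whichever null was intended and must be corrected before analysis. The interval method is misdescribed, with negligible numerical effect.

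**What to change.** Choose one null and make Table 2, Outcomes {12} and Sample size {14} agree on it.

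- **If the null is no difference:** keep the chi-square test from prop.test, and delete the margin hypotheses from Table 2 and the margin from the primary outcome. Either describe the interval as Wald with continuity correction, or replace it with Newcombe's or the Miettinen-Nurminen interval.
- **If the null is a 20-point margin:** replace prop.test with a score test for a non-zero risk difference (Farrington-Manning or Miettinen-Nurminen) at a null difference of 0.20. Call it one-sided with its alpha stated, and take the decision from the matching interval. The sample-size statement must then be redone, because a true 20 points would be the null boundary.

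In both cases give the interval at the level that matches the corrected alpha; a 95% interval does not match a two-sided 0.025. State separately what endpoint 2.1 uses, since it inherits this method.

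The cost is a few lines of Table 2 and, for the margin option, a different R function and a revised power statement. No data collection changes. The choice should be made and recorded before outcome data are compared between groups.
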